#### Secondary endpoints

i)*To compare LiverMultiScan™ image interpretations with clinical outcome after surgery in three domains: post-operative liver function, surgery-specific complication rate and overall complication rate*.

This analysis will use a combination of statistical modelling techniques (e.g. logistic regression) and machine learning techniques (e.g., random forest and tensor flow) to identify the combination of MRI-derived measurements (e.g., LIF, proton density fat fraction, diffusion measurements) that best predict post-operative liver function, or classify patients based on complication rate. Derived models will be cross-validated using leave-*x*-out cross-validation to avoid over-fitting of the model and improve applicability to external populations.

The performance of classification models will be quantified by the area under the receiver operator curve (AUROC) along with the sensitivity, specificity, positive predictive value and negative predictive value for the most appropriate operating point. The statistical significance of any differences in MRI-derived measures of liver health between the different classes will be determined using the most appropriate test based on the Normality of the distributions and the number of groups being compared (e.g., t-test if comparing two Normally-distributed samples; ANOVA if comparing multiple Normally-distributed samples; Kruskal Wallis if comparing non-Normally-distributed samples). The performance of the regression models will be quantified using the appropriate correlation test (e.g., Pearson correlation if normally-distributed; Spearman’s rank correlation if not, or non-linearly correlated).ii)*To compare LiverMultiScan™ image interpretations with histological findings in the resected specimen in four domains: fibrosis, inflammation, fat content and iron load*.iii)*To evaluate LiverMultiScan™ image interpretations with post-operative length of stay*.iv)*To evaluate LiverMultiScan™ image interpretations in the liver regeneration phase*.v)*To identify additional biomarkers of liver health*.

This analysis will use a combination of statistical modelling techniques (e.g., logistic regression) and machine learning techniques (e.g., random forest and tensor flow) to identify those clinical and image-derived parameters being collected as part of the study that have utility in predicting liver health.vi)*To evaluate whether LiverMultiScan™ can add information as to the nature of the liver tumour*.

This endpoint will be evaluated using the same analysis techniques described for the 1st secondary endpoint above to identify and calculate the utility of MRI-derived measurements for characterising liver tumour tissue.vii)
*To evaluate post-intervention cholangiopathy and biliary regeneration with quantitative MRCP*

This endpoint will use quantitative MRCP analysis technology to characterise the regeneration of biliary anatomy in the regenerating liver. This will be a descriptive analysis evaluating the change in intra-hepatic biliary volume, duct diameter and number of branches as the liver regenerates.

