### Intervention

No change in treatment, intervention or randomisation is proposed in the present study.

Eligible participants who have given informed consent will be asked to attend the local research facility for an initial study visit during which baseline clinical assessments, blood tests, and Liver*MultiScan*™MR imaging will be undertaken. Participants in the main study cohort will attend on a second occasion in the post-operative/post-TACE period (total 2 visits and scans). For participants who are enrolled in either of the nested study cohorts (i.e. those undergoing pre-operative chemotherapy or PVE as an adjunct to surgery), an additional scan visit will be required (total 3 visits and scans). An additional 6-month period will follow to complete the post-operative scans of the final recruited participants.

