#### Summary of clinical data to be collected

A full set of the data fields being collected has been exported from the data collection tool and is provided as Additional file 1.

At initial visit:Demographic and general clinical background information,Information regarding the primary liver lesion, and if liver metastases, information regarding the primary tumour,Information relevant to background liver disease/function,Information regarding the proposed surgery/intervention.

At interim visit: (in those having a second pre-operative scan after a period of adjuvant (to the colon primary), neoadjuvant or downstaging chemotherapy; or after PVE):5.Information regarding the interim therapy received including adverse effects and complications.

At operation/TACE:6.Details of surgery/TACE procedure, including weight of resected specimen.

At post-op visit:7.Information regarding recovery from surgery or TACE procedure, including complications and post-op liver function.

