### Primary endpoint

*To determine ability of LiverMultiScan™ to predict risk of post-operative morbidity and mortality by measuring the correlation between the pre-operative liver health assessment score and the post-operative risk score*.

This analysis will measure the correlation between two continuous variables. The first variable will be the FLR volume weighted by the liver inflammation and fibrosis (LIF) score. This weighting will effectively decrease the FLR with increasing LIF score. The second variable will be the composite post-operative risk score as defined by Hyder and colleagues [12]. The distribution of both variables will be tested for Normality (e.g., with the Kolmogorov-Smirnov test) and the correlation calculated with the appropriate test (e.g., Pearson correlation if Normally-distributed; Spearman’s rank correlation if not, or non-linearly correlated).

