### Statistical analysis

#### Sample size

The sample size is pragmatic determined by the duration of the study and recruitment rate. We estimate the following sample size *n* = 100 per site (*n* = 200 total) which includes the nested cohort of *n* = 20 per site (*n* = 40 total). For the primary endpoint, this sample size would allow us to detect a minimum correlation coefficient of 0.2 with a 5% level of significance and power of 80% using a two-tailed test. Furthermore, this sample size will support the evaluation of the secondary endpoints, allowing us to account for any confounding factors (for example, post-operative length of stay may be influenced by lower discharge rates on weekends).

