## Discussion

Liver function can be regarded as the product of the total volume of hepatocytes and the health of those hepatocytes. After hepatectomy, a minimum level of liver function is necessary for survival. At present, that projected liver function is based almost entirely on the estimated FLR volume [13, 14], with most surgical teams adopting minimum thresholds for FLR of approximately 25% in normal livers, and 40% in cirrhotic livers [15]. Ideally, projected future liver function should be calculable as the product of the FLR volume and a continuous variable measure of hepatocyte function. At present, assessment of the FLR relies on computed tomography (CT) volumetric measurement combined with a crude estimate of hepatocyte function based on clinical judgment and gleaned from surrogate markers of liver function based on blood tests. Liver fat content (steatosis) can be measured on CT, or more accurately with magnetic resonance imaging (MRI) [16]. However, hepatic fibroinflammatory disease, which has been shown to correlate with overall and liver-related morbidity after resection [17], typically requires an invasive biopsy to diagnose accurately. Therefore, a preoperative non-invasive investigation that provides the estimated FLR and a validated measure of hepatocyte performance will be an important advance in the safety assessment of patients considering liver surgery.

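### Secondary endpoint (i) can show that MRI is associated with post-operative liver function, but not that it adds anything to the baseline blood tests the study already collects

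*Protocol article*

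**What the plan says.** In the protocol article, the data analysis plan for secondary endpoint (i) uses regression and machine learning "to identify the combination of MRI-derived measurements (e.g., LIF, proton density fat fraction, diffusion measurements) that best predict post-operative liver function", or to classify patients by complication rate. Every example predictor is an imaging measure. Classification models are judged by AUROC, sensitivity, specificity and predictive values, and regression models by a Pearson or Spearman correlation. Leave-x-out cross-validation is planned. No baseline-only model is named as a comparator.

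The pre-operative information exists. Blood tests are part of the initial visit (Intervention). The summary of clinical data lists, at that visit, "Information relevant to background liver disease/function" and, at the post-operative visit, "Information regarding recovery from surgery or TACE procedure, including complications and post-op liver function".

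The Background presents the scan as an additional measure of liver health before hepatectomy. The Discussion says that present practice combines CT volumetry with an estimate of hepatocyte function from clinical judgement and "gleaned from surrogate markers of liver function based on blood tests".

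**The concern.** A patient whose liver works poorly before the operation is likely to have poor function after it, and may also have abnormal MRI measures. An MRI-only model can then perform respectably because it recovers what the pre-operative bloods already showed. AUROC or a correlation computed on that model cannot separate this from new information supplied by the scan. Cross-validation guards against over-fitting and does not address it.

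The difference matters because of the use the article has in mind. It would take success as support for multiparametric MRI within an enhanced pre-operative assessment. A team that already has the blood results needs to know what the scan adds to them, and endpoint (i) as specified does not produce that comparison.

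**Working it through.** **The plan's own figure.** Under Sample size, 200 patients are said to suffice to "detect a minimum correlation coefficient of 0.2 with a 5% level of significance and power of 80% using a two-tailed test". By Fisher's z, n = ((1.960 + 0.842)/atanh 0.2)² + 3 = (2.802/0.2027)² + 3 = 194. With n = 200, power at r = 0.2 is 81.2%. The stated figure reproduces. It concerns the primary endpoint only; the article gives no figure for endpoint (i).

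**Inputs for the illustration.** From the document: n = 200 and a two-sided 5% level. Assumed, because the document gives neither: a, the MRI-to-baseline correlation, and b, the correlation of baseline with post-operative function, each between 0.3 and 0.5.

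**Step 1: unadjusted correlation when MRI adds nothing.** If MRI relates to post-operative function only through baseline function, the unadjusted correlation is r = a × b. The chance that it is significant is approximately Φ(√197 × atanh r − 1.960).

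| a | b | r = a × b | √197 × atanh r | Chance of significance |
|---|---|---|---|---|
| 0.3 | 0.3 | 0.09 | 1.27 | about 25% |
| 0.3 | 0.5 | 0.15 | 2.12 | 56% |
| 0.4 | 0.5 | 0.20 | 2.85 | 81% |
| 0.5 | 0.5 | 0.25 | 3.58 | 95% |

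The third row equals the correlation of 0.2 for which the study is sized.

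**Step 2: the same data with baseline function in the model.** The partial correlation is (r − a × b)/√((1 − a²)(1 − b²)), which is zero here. In 4,000 simulated studies per setting, at (0.3, 0.3), (0.3, 0.5) and (0.5, 0.5), the unadjusted correlation was significant in 25%, 57% and 95%, and the partial correlation in 5.0%, 4.6% and 5.3%. If the worst 15% of outcomes are taken as events (also an assumption), the mean AUROC of the redundant MRI measure was 0.55, 0.58 and 0.63.

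**Step 3: what adjustment does to power.** Take an unadjusted r of 0.2 and use the same partial-correlation formula, with one further degree of freedom removed.

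- MRI uncorrelated with baseline (a = 0), b = 0.5: partial r = 0.2/√0.75 = 0.231, power 91% against 81% unadjusted.
- a = 0.1, b = 0.3 to 0.7: partial r = 0.17 to 0.18, power 69% to 74%.
- a = 0.3, b = 0.5: partial r = (0.2 − 0.15)/√(0.75 × 0.91) = 0.061, power about 14%.

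Break-even is at a of about 0.03, 0.05 and 0.08 for b = 0.3, 0.5 and 0.7. Beyond that, adjustment lowers power.

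**The case against.** The best reply is that the article is a condensed document and is silent rather than wrong. The sample size section says that 200 patients allow confounding factors to be taken into account in the secondary endpoints, and covariate lists commonly sit in a full protocol or SAP that is not shown. This stands in part: nothing in the article excludes baseline function, and a reader should not infer that the investigators have decided against it. But the article does not leave the predictor set open. It names imaging measures for endpoint (i), whereas for endpoint (v) it names clinical and image-derived parameters together, for a different target (liver health). The remark on confounders has only one example, weekend discharge and length of stay, and names no baseline-only comparator.

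The second reply is that an MRI-only model tracking baseline dysfunction still predicts post-operative function, so reporting it is truthful, and that the study describes itself as proof of concept. This stands. A reader might take the 25% to 95% as inflated type I error. They are not: in those scenarios the unadjusted correlation truly differs from zero, and the roughly 5% after adjustment tests a different null hypothesis.

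A reader might also extend the point to the primary endpoint, where "This analysis will measure the correlation between two continuous variables" and no baseline term appears. The documents do not support calling that a defect of the same kind. The outcome is a composite post-operative risk score, and no pre-operative version or list of components is given. Likewise, the article does not say that the background liver information at the initial visit is the same measure as the post-operative one.

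**Conclusion.** The point holds for secondary endpoint (i), as a limit on what its results can support. The named predictors and metrics can show association with post-operative liver function. They cannot show that the scan improves on baseline bloods, although the data needed to examine this are collected and the study's rationale turns on it.

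The size depends wholly on assumed correlations. With both between 0.3 and 0.5, a scan adding nothing would give a significant unadjusted correlation in about 25% to 95% of studies at n = 200.

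Three stronger conclusions should not be drawn: that the MRI-only result would be false, that the primary analysis or sample size is invalid, or that omitting baseline function wastes power. The last holds only when MRI and baseline function are almost uncorrelated, which runs against the overlap that gives rise to the concern.

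**What to change.** In the analysis plan for secondary endpoint (i), for each model of post-operative liver function:

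- fit a baseline-only model holding the pre-operative liver function measures from the initial visit;
- add the MRI measures and report the gain, as the change in cross-validated AUROC or R-squared within the cross-validation already planned, or as a partial correlation;
- base any claim of added value over current assessment on that gain, and report the MRI-only results as association.

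Leave the primary correlation and the sample size unchanged. A partial rank correlation of the HepaT1ca score with the post-operative score, adjusted for pre-operative liver function, is at most an optional supportive analysis.

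The cost is a few sentences and some extra model fits, with no new visits, samples or patients. The downside is that the adjusted association will usually be smaller, with lower power, when MRI and baseline bloods overlap. The gain should therefore be reported with its confidence interval, and a non-significant gain should not be read as proof that the scan adds nothing.

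### As worded, the cross-validation of the prediction models may leave optimistic accuracy figures, gives no support for external applicability, and is paired with a regression metric blind to miscalibration

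*Protocol article*

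**What the plan says.** The text is in the protocol article, Data analysis plan, Secondary endpoints, item (i).

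- **Search.** Logistic regression, random forest and a neural-network toolkit are to be used "to identify the combination of MRI-derived measurements (e.g., LIF, proton density fat fraction, diffusion measurements) that best predict post-operative liver function", or to classify patients by complication rate. The number of candidate measures is not given.
- **Validation.** The next step reads "Derived models will be cross-validated using" a leave-x-out scheme. Its stated purpose is "cross-validation to avoid over-fitting of the model and improve applicability to external populations".
- **Classification metrics.** AUROC is reported together with "sensitivity, specificity, positive predictive value and negative predictive value for the most appropriate operating point". No cut-off is fixed in advance, and the data used to choose it are not named.
- **Regression metrics.** Performance is quantified by a Pearson or Spearman correlation.

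Item (vi), on tumour type, reuses the techniques of item (i). Item (v) makes a similar search over clinical and imaging parameters. Setting names two UK centres, and no external or held-back data set is described.

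**The concern.** Cross-validation gives an honest estimate only of what is repeated inside its loop. If the best combination of measures is found on all patients and only the final model is refitted fold by fold, the held-out patients have already helped to choose the predictors. A cut-off chosen on the same held-out predictions that are then used to report sensitivity and specificity adds a second layer of optimism. The wording puts the derived model, rather than its derivation, through cross-validation, so it permits both.

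The stated rationale also claims too much. Leave-x-out within one cohort estimates performance in patients like those sampled. It is not evidence about other populations, and it measures over-fitting rather than preventing it by itself.

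Finally, a correlation does not show whether predicted values are right in absolute terms. The abstract and the Background both give personalised operative risk assessment as the goal, and that goal needs predictions of the right size. What is at stake is that measures with little or no predictive value could be reported as useful, or that well-ranked but wrongly scaled predictions could pass as accurate.

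**Working it through.** **1. The plan's own figure.** The article gives no figure for the prediction models. Its only sample-size statement is for the primary correlation: with 200 patients, "detect a minimum correlation coefficient of 0.2 with a 5% level of significance and power of 80" per cent, two-tailed. By Fisher's z:

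- n = ((1.960 + 0.842) / atanh(0.2))² + 3 = (2.802 / 0.2027)² + 3 = 193.97, so 194 patients.
- Power at n = 200 = Φ(0.2027 × √197 − 1.960) = 0.812.

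The statement reproduces. It concerns the primary endpoint only.

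**2. Optimism from selection and cut-off choice.** Inputs:

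- From the article: n = 200.
- Assumed, because the article gives none of them: 10, 20 or 50 candidate measures; event rates of 10, 20 or 30%; the five candidates most correlated with the outcome kept; a linear classifier; stratified 10-fold cross-validation.

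No candidate is related to the outcome, so the true AUROC is 0.50 and the true Youden index (sensitivity + specificity − 1) is 0. There were 400 data sets per setting. Results are means.

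| Candidates | Events | AUROC, selection outside loop | AUROC, selection inside | Youden: selection outside, cut-off from held-out predictions | Youden: selection inside, cut-off from held-out predictions | Youden: both inside training folds |
|---|---|---|---|---|---|---|
| 10 | 10% | 0.596 | 0.500 | 0.238 | 0.136 | 0.001 |
| 10 | 20% | 0.570 | 0.498 | 0.175 | 0.105 | −0.005 |
| 10 | 30% | 0.561 | 0.499 | 0.155 | 0.093 | 0.001 |
| 20 | 10% | 0.663 | 0.496 | 0.328 | 0.142 | −0.003 |
| 20 | 20% | 0.620 | 0.494 | 0.241 | 0.102 | −0.011 |
| 20 | 30% | 0.606 | 0.498 | 0.214 | 0.094 | −0.004 |
| 50 | 10% | 0.727 | 0.498 | 0.412 | 0.147 | 0.001 |
| 50 | 20% | 0.675 | 0.499 | 0.317 | 0.114 | 0.001 |
| 50 | 30% | 0.652 | 0.498 | 0.278 | 0.094 | 0.000 |

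A separate simulation used logistic regression with the best 3 to 5 of 10 to 40 noise inputs at the same event rates. It gave 0.57 to 0.70 with selection outside the loop and 0.48 to 0.50 inside.

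Two things follow. Selection outside the loop inflates AUROC in every setting, more so with more candidates and fewer events. Nesting the selection alone is not enough: a cut-off chosen on the held-out predictions still yields a Youden index of 0.09 to 0.15 from noise. With both steps in the training folds it is about 0.

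**3. External applicability.** Set the purpose clause beside Setting: patients come from two centres, and each left-out patient comes from the same two centres as the training patients. Nothing in the scheme samples another population.

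**4. Correlation as the regression metric.** For any a and any b > 0, corr(a + b × prediction, outcome) = corr(prediction, outcome). Spearman's coefficient is unchanged by any increasing transformation. A model that doubles every prediction therefore scores the same as the correct one. Root mean squared error and the calibration slope would differ.

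**The case against.** A reader might infer that the protocol fixes a biased order, with combination and cut-off chosen on all the data first and cross-validation last, so that inflated results are certain. The document does not support this. That order is read from a single word about models having been derived, and the operating point is not placed in any order relative to cross-validation. The text is compatible with a fully nested procedure, which removed the bias in the simulation.

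It can also be said that fold nesting and threshold rules usually sit in an analysis plan or full protocol, and neither is shown. That stands: their absence from a journal article is not the point. What remains is that the most direct reading of the published wording is the unprotected one.

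The simulated sizes depend on inputs the article does not give. It names three MRI measures as examples and no candidate count, and random forests need no outcome-based screening beforehand. This stands too: the figures show what happens if selection is left outside the loop, not that this is planned.

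Calling the external-applicability clause simply untrue would go too far. It does not claim external validation, and limiting over-fitting can help a model to generalise. Unsupported is the fair word.

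Lastly, these are secondary analyses in a proof-of-concept study that changes no treatment. That limits the weight of the point but does not answer it.

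**Conclusion.** The point holds in conditional form. Classification performance may be optimistic unless every data-driven choice is repeated within the training folds. Under the assumptions above, the excess in AUROC with no signal is roughly 0.06 to 0.23 (0.56 − 0.50 to 0.73 − 0.50). With selection also outside the loop, a cut-off taken from the held-out predictions gives a Youden index of 0.16 to 0.41 where the truth is 0.

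Two parts rest on what the article states and need no simulation: the external-applicability clause is unsupported, and correlation alone cannot reveal miscalibrated regression predictions. Further detail in an analysis plan could settle the conditional part, but the published rationale would still need correcting. The primary correlation and its sample size are not affected. This should be changed before any model results are reported.

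**What to change.** - State that variable selection, choice of learner, tuning and cut-off choice are repeated within each training fold (nested, stratified, repeated cross-validation), and that all reported metrics come from held-out predictions with confidence intervals. Apply the same rule to items (v) and (vi).
- Compute sensitivity and specificity over all held-out patients, each classified with the cut-off from its own training fold. At an assumed 10% event rate, 200 patients give 20 events, or 2 per fold in ten folds, so sensitivity within a single fold could only be 0, 0.5 or 1.
- Add calibration intercept and slope, and root mean squared error for regression models.
- Replace the external-applicability clause with a statement that this is internal validation, and add an exploratory leave-one-site-out check. Its precision is low: 100 patients per site at 10 to 30% events means 10 to 30 events in the test site. For a sensitivity of 0.5, the 95% half-width is about 1.96 × √(0.25/10) = 0.31 down to 1.96 × √(0.25/30) = 0.18. Training on one site would have equally few events.

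The cost is more computing, a paragraph of text and probably less favourable reported performance. No new data are needed.

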#### Secondary endpoints

To compare Liver*MultiScan*™image interpretations with clinical outcomes after surgery or TACE in three domains: post-operative liver function, surgery-specific complication rate, and overall complication rate. The Clavien-Dindo classification (using all 5 grades) of morbidity will be used, in addition to free text descriptors of complications. Morbidity and mortality at 30 days and 90 days after surgery will be reported.To compare Liver*MultiScan*™image interpretations with histological findings in the resected liver specimen in four domains: fibrosis, inflammation, fat content and iron loadTo evaluate Liver*MultiScan*™image interpretations correlated with post-operative length of stayTo evaluate Liver*MultiScan*™interpretations in the liver regeneration phaseTo identify prognostic biomarkers of liver healthTo evaluate whether Liver*MultiScan*™can add information as to the type of liver tumourTo evaluate biliary pathology after chemotherapy and biliary regeneration after surgery with quantitative MRCP

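### Complications are recorded on the ordered Clavien-Dindo scale but analysed as undefined classes, under a test-selection rule that takes no account of grade order

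*Protocol article*

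**What the plan says.** The protocol article lists the secondary endpoints under Measurements. On complications it states: "The Clavien-Dindo classification (using all 5 grades) of morbidity will be used". Complications are therefore graded on an ordered scale. With patients who have none, there are six ordered categories.

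The Data analysis plan, secondary endpoint (i), aims to find the MRI measures that predict post-operative liver function "or classify patients based on complication rate". The number of classes and their cut-points are not given. Classification models are judged by AUROC, sensitivity, specificity and predictive values. Differences in MRI measures between classes are tested by the "most appropriate test based on the Normality of the distributions and the number of groups being compared". The examples are a t-test for two groups, then "ANOVA if comparing multiple Normally-distributed samples; Kruskal Wallis if comparing non-Normally-distributed samples".

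Rank correlation does appear in the same item, but for another purpose: "The performance of the regression models will be quantified using the appropriate correlation test".

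The Sample size section gives power only for the primary correlation. For the secondary endpoints it offers a general assurance and no figure.

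**The concern.** The study's hypothesis has a direction: poorer liver health before surgery should go with a worse course afterwards. Across complication grades that is a trend. ANOVA and Kruskal-Wallis give the same result if the grade labels are shuffled, so they cannot draw on that direction and they spread the signal over several degrees of freedom. A two-class split keeps one cut of the scale and discards the rest.

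The selection rule names two criteria, and ordering is not one of them. An analyst who applies it to graded complications is led to a test that ignores information already collected. At stake is a greater chance of missing a real association with an observed patient outcome. The sample size is described as pragmatic, so it cannot readily be raised to make up for an inefficient test.

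**Working it through.** **1. The plan's own figure.** The inputs, from the Sample size section, are n = 200, the aim to "detect a minimum correlation coefficient of 0.2", and this "with a 5% level of significance and power of 80% using a two-tailed test". By Fisher's z, n = ((1.960 + 0.842)/atanh(0.2))² + 3 = (2.802/0.2027)² + 3 = 193.97, so 194. Power at n = 200 is Φ(0.2027 × √197 − 1.960) = 81.2%. The figure reproduces. It concerns the primary endpoint only; nothing comparable is stated for complications.

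**2. Cost of ignoring order, without a grade distribution.** Suppose a one-degree-of-freedom trend test has 80% power. Its noncentrality is (1.960 + 0.842)² = 7.85. If the trend carries all the signal, comparing k unordered classes spends k − 1 degrees of freedom on the same noncentrality:

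| Classes | Power | Patients needed to match the trend test at 200 |
|---|---|---|
| 3 | 71% | 246 |
| 4 | 64% | 278 |
| 5 | 60% | 304 |
| 6 | 56% | 327 |

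**3. Simulation at 200 patients.** The assumptions, none of them from the documents, are a Normal MRI measure and a latent severity correlated r with it and cut into none and grades I to V. The value r = 0.20 is borrowed from the primary endpoint; 0.25 is a second value. There were 1,500 runs per row. The ordered test is Spearman on grade and the two-class test is Mann-Whitney. Entries are power in percent.

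| none/I/II/III/IV/V (%) | r | Ordered | Any vs none | III or above | Kruskal-Wallis, all | ANOVA, all |
|---|---|---|---|---|---|---|
| 60/10/15/9/3/3 | 0.20 | 66.5 | 60.1 | 44.6 | 39.8 | 43.1 |
| | 0.25 | 83.1 | 77.7 | 60.1 | 62.0 | 63.3 |
| 50/15/18/10/4/3 | 0.20 | 70.6 | 60.4 | 45.5 | 43.5 | 45.7 |
| | 0.25 | 85.8 | 78.8 | 64.3 | 62.8 | 66.5 |
| 70/8/11/7/2/2 | 0.20 | 59.6 | 54.9 | 39.2 | 34.5 | 37.7 |
| | 0.25 | 78.6 | 74.7 | 53.7 | 51.7 | 55.5 |
| even over six | 0.20 | 76.9 | 45.8 | 61.9 | 50.5 | 52.9 |
| | 0.25 | 90.2 | 64.1 | 79.7 | 72.3 | 74.3 |

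With no association, every test rejected in 3.7% to 5.9% of runs, so the comparison is fair.

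**4. Simulation at 160 patients.** The number 160 is also an assumption, as are the grades 55/15/12/10/5/3%. With 3,000 runs, ordered, III or above, Kruskal-Wallis and ANOVA gave 59.2, 38.8, 33.8 and 35.7% at r = 0.20, and 78.5, 56.2, 50.8 and 54.9% at r = 0.25. A second set of runs of this scenario gave ordered against any-versus-none as 58 against 52% at r = 0.20, and 78 against 73% at r = 0.25.

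**5. Losses under the skewed distributions.**
- Any versus none: from 78.6 − 74.7 = 3.9 to 70.6 − 60.4 = 10.2 points.
- III or above: from 59.6 − 39.2 = 20.4 to 70.6 − 45.5 = 25.1 points.
- All grades by ANOVA or Kruskal-Wallis: from 85.8 − 66.5 = 19.3 to 78.5 − 50.8 = 27.7 points.

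The simulation error of one power figure is at most √(0.25/1500) = 1.3 points. I therefore take the lower ends of the last two ranges as about 18.

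**6. Is Spearman a fair stand-in?** Fitting the proportional-odds model itself, at n = 200 and r = 0.20, gave power close to Spearman: 67 to 72% for the ordered analyses. The alternatives gave 60% for any versus none, 57% for Kruskal-Wallis on three classes, 48% for III or above and 42% for Kruskal-Wallis on all six categories.

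**The case against.** A reader might infer that the plan commits to ANOVA or Kruskal-Wallis across the five grades and so gives up a large share of its power. The article does not support that. The tests are introduced as examples, a t-test for two groups is among them, and the classes are never said to be the grades. A large loss arises only if all grades are compared as unordered groups or the cut falls high on the scale. With any versus none under skewed grades it is modest.

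Other points on that side also carry weight:
- The logistic regression named for this endpoint is not said to be binary, so an ordinal form is not excluded, and an analysis plan that is not shown may specify one.
- The same techniques are applied to tumour type under endpoint (vi), where order-free tests are suitable.
- The article follows STARD and wants an operating point, for which a clinically defined class is legitimate.
- The 160 patients and every grade distribution are assumptions. The 40 in the Sample size section is the nested chemotherapy and PVE cohort, so 160 cannot be read as the number resected.

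These points limit the size of the claim. They do not remove it, because the selection rule itself is stated, it rests on Normality and number of groups, and no method named for complication classes uses grade order.

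**Conclusion.** The point holds as a mismatch between an ordered outcome and a test-selection rule that overlooks order. The possible loss is about 4 to 10 points for any versus none, about 18 to 25 for grade III or above, and about 18 to 28 for all grades by ANOVA or Kruskal-Wallis. These ranges assume a monotone association, skewed grades, latent r of 0.20 to 0.25 and 160 to 200 patients. They do not carry over to every distribution: with grades spread evenly, any versus none loses more (76.9 − 45.8 = 31.1 points at r = 0.20) and a split at III loses less (76.9 − 61.9 = 15.0). The ordered analysis had the highest power under every class definition tried.

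This is a worthwhile, inexpensive improvement to a secondary endpoint. It is no evidence that the study is underpowered for its primary correlation, whose stated figure reproduces.

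**What to change.** For secondary endpoint (i), state that the association between the MRI measure and complication severity is tested by a method that uses grade order, from 0 (none) to 5 (death). Proportional-odds regression is a natural choice, reporting the odds ratio per standard deviation of the MRI measure with its 95% CI. Spearman correlation with grade can serve as a check. Allow sparse top grades to be merged: at an assumed 2 to 3% of 200 patients, the highest grade would hold only 4 to 6.

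Keep the classification models and AUROC, for a class defined in advance, as the supporting diagnostic-accuracy summary. Keep the order-free tests for nominal outcomes such as tumour type.

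The cost is wording and a check of the proportional-odds assumption. No new data or patients are needed.
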